### Measures

All measures used over the course of the study at the different measurement points are listed in Fig. 1.

#### Primary outcome measures

##### Montgomery-Asberg Depression Rating Scale (MADRS) [63]

The MADRS is one of the most commonly used rating scales for assessing the core symptoms of depression [64]. It is conducted as a structured clinician-rated interview consisting of 10 items: apparent sadness, reported sadness, inner tension, reduced sleep, reduced appetite, concentration difficulties, lassitude, inability to feel, pessimistic thoughts, and suicidal thoughts. Each item is rated on a 7-point scale ranging from 0 to 6 with higher scores indicating greater severity of symptoms. A score greater than 31 on the MADRS indicates severe depression, whereas a score of 10 or below indicates remission [65, 66]. Originally, the scale was published without wording suggestions for clinicians to help them collect the information required to rate the items. For this reason, we used the *structured interview guide for the Montgomery-Asberg Depression Rating Scale (SIGMA)* [64]. The SIGMA is a structured interview guide that offers a selection of different questions for each of the 10 items with good to excellent interrater reliabilities [64].

#### Secondary outcome measures

##### Generalized Anxiety Disorder Scale-7 (GAD-7) [67]

The GAD-7 is used to assess anxiety. It is a short self-report questionnaire with seven items for assessing how often participants have experienced the seven core symptoms of generalized anxiety disorder during the last 2 weeks. Items are rated on a 4-point scale ranging from 0 (*not at all*) to 3 (*nearly every day*). Total scores can range from 0 to 21, with scores ≥ 5 indicating mild anxiety symptoms, scores ≥ 10 moderate anxiety symptoms, and scores ≥ 15 severe anxiety symptoms [67].

#### Skala zur Allgemeinen Selbstwirksamkeit (SWE) [68, 69]

The SWE is used to measure self-efficacy, which refers to the subjective belief that one is able to cope successfully with difficult situations. The questionnaire consists of 10 items that are answered on a unidimensional 4-point scale ranging from 1 (*not true*) to 4 (*exactly true*). Individual test scores can range from 10 to 40, with higher scores indicating higher self-efficacy [68, 69].

#### Sense of Coherence scale (SOC) [70, 71]

The short nine-item version of the SOC (SOC-L9) is used to measure participants’ sense of coherence, which is defined as a global belief concerning the extent to which individuals have a general enduring and dynamic sense of confidence that they are able to make reasonable and probable predictions about developments in their internal and external environment [70]. The nine items are rated on a unidimensional 7-point scale ranging from 1 to 7 with different verbal labels at each end (e.g., frequency, agreement). Scores range from 9 to 63, with higher scores implying a higher sense of coherence [70, 71].

#### Internal-External Locus of Control Scale (IE-4) [72]

The IE-4-scale is used to measure locus of control, containing a subscale for internal locus of control and a subscale for external locus of control with two items each. An internal control belief is associated with the extent to which a person is convinced that they are able to control events, whereas an external control belief refers to the extent to which a person believes that events and experiences are left to fate or chance or are controlled by other people over whom they have no control [72]. The items are rated on a 5-point response scale ranging from 1 (*not at all true*) to 5 (*completely true*). The scores are averaged for each subscale, resulting in scores that range from 1 to 5. Higher scores indicate higher internal or external locus of control [72].

#### State Mindfulness Scale for Physical Activity (SMS-PA-12) [73, 74]

The SMS-PA-12 is used to measure state mindfulness of the mind and of the body. The first refers to the concept of self-regulation of attention to being present without judgment as well as openness to, curiosity about, and acceptance of mental and physical experiences, whereas the latter describes how much attention people pay to their physical effort or bodily engagement. The SMS-PA-12 consists of 12 items with the subscales mindfulness of the mind and mindfulness of the body, each of which contain six items. All items are rated on a 5-point scale ranging from 0 (*not at all*) to 4 (*very much*). The SMS-PA-12 supports the use of a single score for overall state mindfulness as well as two separate scores for the subscales and has up to now not been validated in the German language [73, 74].

#### Multidimensional State Mindfulness Questionnaire (MSMQ) [75]

The MSMQ is used to assess state mindfulness. Following a factor analysis, state mindfulness in the MSMQ can be viewed as the within-person component of mindfulness, contrary to trait mindfulness, which is described as the between-person component. Fifteen items are rated on a 7-point scale ranging from 0 (*does not apply at all*) to 6 (*applies completely*). The items provide information about three distinguishable facets of mindfulness: acting with awareness, nonjudgmental acceptance, and present-moment attention [75].

#### Physical Activity, Exercise, and Sport Questionnaire (Bewegungs- und Sportaktivität Fragebogen; BSA-F) [76]

The BSA-F is used to record the frequency, duration, intensity, and type of physical activities that participants engage in with respect to movement and sports. The scale is divided into three subscales that measure activities involving movement at work, activities involving movement during free time, and sports activity. Only the first and third subscales are included in the current study. Items measuring movement are answered on a 4-point scale ranging from 0 (*none*) to 3 (*a lot*). Sports activity is assessed with an open question about the type, frequency, and duration of sports and exercise that participants have engage in over the past 4 weeks. The data will be summarized in an index of sports activity [76].

#### Fragebogen zum Erleben von therapeutischen Prozessen in der Gruppe (FEPiG) [77]

The FEPiG is deployed to detect the factors of influence of the group therapies by assessing the experience of the therapeutic processes and the acceptance of the form of therapy. In the current study, only 30 of the 42 items are being used with an additional question about whether the participant would recommend the specific group therapy. The items are answered on a 5-point scale ranging from 0 (*not at all true*) to 4 (*completely true*). Assessable factors of influence are interpersonal learning, group cohesion, goals and tasks, catharsis, bonding with therapists, and problem actualization [77].

#### Baseline® hydraulic hand dynamometer [78]

The hydraulic dynamometer is deployed to measure hand or grip strength, which has been demonstrated to be a valid measure of muscle strength in general [79]. The handheld device is used with the left and right hands consecutively, and participants are instructed to squeeze with maximum force [78]. The values for each hand are compared with a sex- and age-specific norm table [80, 81].

#### McGill’s torso muscular endurance test battery [82]

The torso muscular endurance test battery measures core stability. It consists of the following three subtests: trunk flexor endurance test, trunk lateral endurance test, and trunk extensor endurance test. The goal of each exercise is to hold the required position for as long as possible while the time is measured with a stopwatch. The results are presented as three different ratios that can be rated as either good or poor: flexion to extension ratio, right-side bridge to left-side bridge ratio, and side bridge (each side) to extension ratio [82].

#### Analysis of blood biomarkers

Blood samples are being collected in 9-ml-serum and 9-ml-EDTA-plasma vials at both t0 and t1, centrifuged, and stored as serum and plasma aliquots, respectively, at – 80 °C. After lysis or erythrocytes, pellets of peripheral blood mononuclear cells will be frozen dry or stabilized with RNA later. The blood samples will be analyzed for the concentration of biomarkers, such as osteocalcin, growth and immune factors using commercial antibody-based ELISAs, and other detection methods. Enzyme activities of sphingolipid metabolism will be determined by established assays using fluorescently-labeled substrates [83]. Gene expression analysis will be performed by quantitative real-time PCR.

#### Body fat scale

We are using the personal scale to measure participants’ BMI, body fat percentage, and muscle percentage during the physical examinations.

#### Cognitive Reflection Test (CRT-3) [84, 85]

The CRT-3 is used to assess cognitive processing and performance on heuristics-and-biases tasks. It measures the tendency to engage in the kind of reflection that leads to the correct answer instead of choosing the prepotent but incorrect response alternative. The test consists of three questions [84, 85].

#### Qualitative interviews

In computer-assisted qualitative interviews, Grawe’s factors of influence (e.g., resource activation, problem actualization, motivational clarification, problem solving, and therapeutic relationship) [86] are being assessed for both IGs. The interviews are based on guidelines for semi-structured interviews that are being conducted to collect additional potential factors of influence that go beyond the previously mentioned concepts: previous experiences with (group) therapies; individual changes throughout the intervention; feelings related to the group, the therapists, and the therapy itself; negative experiences or effects; and potential barriers. In accordance with Mayring’s [87] specifications, a qualitative content analysis that follows the principles of thematic analysis [88] will be conducted to evaluate all qualitative data.

#### Other variables

During enrollment, interested people are participating in a computer-assisted diagnostic video *screening interview* to assess the inclusion and exclusion criteria before being told whether they can participate in the study. The interviewer assesses the following data: *age*, *sex*, *height*, and *weight* to determine *body mass index* (BMI), *current outpatient group therapy*, *current psycho-pharmacotherapeutic treatment*, *physical limitations*, *psychiatric comorbidities*, *preferences concerning future group allocation* (BPT, MMT, CG), and *depressive symptoms*. The presence of a current depressive episode is measured with a structured interview based on the DSM-V diagnostic criteria [53]. It includes the assessment of the participants’ current depression as well as past episodes and age of onset.

At baseline, further sociodemographic data, such as *family status*, *level of education*, and *current occupation*, are being assessed via a questionnaire. In a video interview, the following additional data are being collected: *current and past psychotherapeutic treatment* (inpatient and outpatient), *experiences with mindfulness and meditation*, and *participation in sports for the treatment of depression*.

*Changes concerning current psycho-pharmacotherapeutic and psychotherapeutic treatment* are being assessed with a video interview shortly after as well as 12 months after the intervention.

*Critical events*, such as injuries, accidents, mental crises, or hospitalization, as well as their intensity (mild, medium, severe), during the intervention period and during the year following the intervention are being assessed shortly after and 12 months after the intervention. The intensity of these events is judged on the basis of the extent of the impact on the participant’s life and the resulting need for treatment.

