	Exclusion criteria: 1. Age < 18 years 2. Presence of current severe mental illnesses that complicate participation in group therapy (e.g., psychosis, mania, current self-injury, acute substance dependence, current suicidality) 3. Physical contraindication for climbing (physical ailments or pregnancy) 4. Body Mass Index (BMI) < 17.5 or > 40 5. Current treatment confounded with study outcomes (participation in psychotherapeutic group therapy, initiation/change in psychotropic medication within 8 weeks prior to the intervention)
15. Study type	Randomized controlled prospective assessor-blinded longitudinal clinical intervention study
16. Date of first enrollment	Began on March 29, 2022
17. Target sample size	120
18. Recruitment status	Ongoing
19. Primary outcome(s)	Depression measured with the Montgomery Asberg Rating Scale (MADRS) score from a third-party assessment in computer-assisted video interviews
20. Key secondary outcomes	Anxiety, self-efficacy, sense of coherence, locus of control, (mind- and body-based) state mindfulness, physical activity, mechanisms of therapeutic change in group therapy, blood concentration of osteocalcin, sphingolipid parameters, growth factors and inflammatory markers, qualitative factors of influence
BPT specific	Hand strength, core stability, BMI, body fat percentage, muscle percentage
MMT specific	Cognitive processing

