#### Masking

Whereas participants are informed about which treatment condition they are allocated to, the interviewers conducting the video interviews and thus assessing the outcomes of the study are blind to the participants’ group allocations. At the beginning of each interview, the participant is reminded to remember the confidential nature of their allocation and not to tell the interviewer which treatment they are receiving.

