## Discussion

In this article, we presented the design for a randomized controlled trial to test the efficacy of two short-term group therapies for outpatients with depression using a mixed methods approach. In addition to quantitative data collection, qualitative data on factors of influence for each intervention will be analyzed. The study could offer important insight into the effectiveness and potential factors of influence of short-term group therapies that have up to now been less well studied than individual therapies [13].

The group therapies that are being investigated in the present study are, first, BPT, whose effectiveness has already been investigated in two RCTs [23, 25] and, second, a newly developed cognitive-based group therapy with mental models.

Both interventions consist of innovative new elements with an effective therapeutic background: BPT includes contents of physical activity and body experience, MMT the element of mental models with a long-term influence derived from research on decision making [30, 31]. As a significant number of patients still do not profit from existing psychotherapies [10], it seems sensible to develop different types of therapies and identify possible factors of influence in order to be able to personalize the therapeutic technique to enhance the benefits of this technique for all at a later stage of development.

During and after the intervention period, participants are free to begin or continue other therapeutic treatments offered by the German health care system without suffering any disadvantages. Previous ongoing treatment plans will not be changed by their participation in this study. Therapeutic treatment outside of the study will be assessed in the video interviews.

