Participation in the BPT is accompanied by a slight risk of injuries; however, this level of risk does not exceed the risks of other physical activities. In a study on sport-climbing injuries, an average number of 0.2 injuries per 1000 h of climbing (which has higher risks of severe injuries than bouldering) occurred in a sample of about 2000 climbers [90]. In our study, bouldering time is limited to a maximum of 10 × 2 h per patient. Hence, severe injuries are not expected. Irrespective of their group allocation, all participants are provided with road and accident insurance while participating in the study. In our previous studies, no SAEs occurred in more than 4000 h of bouldering. Nevertheless, interim analyses of SAEs are being performed on a regular basis in both intervention groups. If any analyses show a cumulation of SAEs in one group, the respective intervention will be terminated.

All participants’ suicidality and capability of collusion are being assessed during the diagnostic screening interview and at all measurement points in the video interviews as part of the MADRS. During the therapy sessions, therapists follow good clinical practice in monitoring for suicide risk. In cases of acute risks, they will establish suicide risk management plans.

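### Treatment changes are collected by video interview at t1 and t2, apparently by the blinded MADRS raters; only a reminder to the participant protects the blind, and the exposure is clearest at t2

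*Protocol article*

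**What the plan says.** **Who is blind.** Under Masking, "the interviewers conducting the video interviews and thus assessing the outcomes of the study are blind" to allocation, while participants know their arm. The stated safeguard is a request made when an interview opens: participants are "reminded to remember the confidential nature of their allocation and not to tell the interviewer which treatment they are receiving".

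**Where the primary outcome is rated.** Table 1 defines it as the MADRS "score from a third-party assessment in computer-assisted video interviews". The Discussion confirms that the MADRS is part of the video interviews by saying that suicidality is assessed "at all measurement points in the video interviews as part of the MADRS".

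**What else is asked by video interview.** Under Other variables, changes in psychotropic and psychotherapeutic treatment "are being assessed with a video interview shortly after as well as 12 months after the intervention". The Discussion adds: "Therapeutic treatment outside of the study will be assessed in the video interviews".

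**Critical events.** The same section lists events "such as injuries, accidents, mental crises, or hospitalization". It gives the times of assessment (after the intervention and 12 months later) but neither the mode nor the assessor.

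**What controls may receive.** Under Control group (CG), control participants who are interested get priority access to outpatient BPT after t1.

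**The concern.** The MADRS is scored by an interviewer, participants cannot be blinded, and the comparator is usual care without any study-specific therapy. Rater blinding is therefore the main protection against biased scoring, and the Discussion counts it among the trial's strengths. Under the stated procedure a participant is asked to keep the study treatment confidential and is then, apparently by the same interviewer, asked which treatments have changed. A truthful answer can reveal the arm. If that happens before the MADRS is scored, the rating is no longer blind.

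There is a possible second cost. A cautious participant might hold back treatment information because of the reminder. The regressions planned under Quantitative measurements to control for additional treatment would then use incomplete data. The document does not show that this happens.

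**Working it through.** The plan gives no figure for this point, so the check sets the statements side by side. One small calculation shows how much weight the injury route can bear.

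**Step 1: is the MADRS rater the person who hears the treatment answers?**
- Masking defines the blinded outcome assessors as those who conduct the video interviews.
- Table 1 and the Discussion place the MADRS in those interviews.
- Other variables and the Discussion place the treatment-change questions in video interviews at t1 and t2.
- Data collection names one group of video interviewers, trained students, and no unblinded second interviewer.

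The plain reading is yes. It remains an inference, because no sentence says that one person asks both sets of items.

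**Step 2: what can the answers reveal?**
- *At t1.* The Discussion limits the questions to treatment outside the study, and every arm may use such treatment. Reporting an antidepressant or individual therapy does not identify the arm. Disclosure would be incidental, for example if someone says that individual therapy was paused because of the study group.
- *At t2.* Priority access to outpatient BPT after t1 is offered to control participants. One who accepts has started a therapy outside the study and should report it. A new BPT course begun after t1 points strongly to the control arm.

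**Step 3: could critical events reveal the arm?** The mode of collection is not given; Data collection lists questionnaires, video interviews and physical examinations. On the article's own figures for injuries:
- Arm size: 40 (Sample size estimation).
- Bouldering time: at most 10 × 2 h = 20 h per patient (Discussion).
- Cited sport-climbing rate: 0.2 injuries per 1000 h (Discussion).
- Exposure: 40 × 20 h = 800 h.
- Expected injuries: 800 × 0.2/1000 = 0.16.
- Chance of at least one (Poisson): 1 − exp(−0.16) = 0.148, about 15%.

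This assumes that the sport-climbing rate applies; minor injuries may be more frequent. Even so, injuries are a minor route, and treatment changes are the main one.

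**Step 4: do other stated measures cover the gap?** Double rating of 10% of MADRS interviews (Data quality management and data protection) checks agreement between raters, not blinding, and covers t0 and t1 but not t2. The reminder reduces spontaneous disclosure but does not resolve the t2 case, where the requested answer is itself informative.

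**The case against.** The strongest case against is that this is operational detail. Item order, separate interviewers and recording of arm guesses belong in a full protocol or interviewer manual, and a journal article condenses these. The treatment questions concern only care outside the study, so a participant can answer them and still follow the reminder.

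Much of this stands. At t1 the two requests are compatible, and an undisclosed manual may already put the MADRS first. The t2 case remains: the article itself creates an outside treatment offered to one arm only, asks about it by video interview and states a single safeguard. That is a tension between stated procedures, not merely an omitted detail.

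Three stronger readings are tempting but not supported:
- *The blinded raters ask about injuries and crises.* The article gives no mode or assessor for critical events.
- *Participants cannot answer without revealing the arm.* At t1 they can, because study therapy is not what is asked.
- *The bias can be sized.* An assumed rater shift of 0.1 to 0.2 SD, set against the article's d of 0.55 to 0.77, would be 0.1/0.77 = 13% to 0.2/0.55 = 36% of the effect. The shift has no basis in the document, so these percentages are illustration and not evidence.

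**Conclusion.** The point holds in a limited form. As described, treatment-change questions at t1 and t2 are put in video interviews run by the people who are to rate the MADRS blind, with only a reminder to the participant as protection. The exposure is incidental at t1 and clearer at t2, for control participants who took up BPT. The t1 comparison is therefore less at risk than the 12-month comparison.

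The size of any bias is not estimable: the document gives neither the number of controls expected to accept BPT nor how often raters would infer the arm. The direction at t2 is also open, since a rater may learn both that the participant was a control and that he or she has since had BPT.

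The conclusion assumes that one interviewer asks both sets of items and that no document outside the article fixes the order. If either assumption is wrong, a clarifying sentence is enough. The change is worth making because it is nearly free and protects the only primary outcome.

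**What to change.** 1. Move the treatment-change items, and critical events if they are asked in the same interview, to the online questionnaire already used at t0, t1 and t2. Alternatively, have the MADRS rated and locked in the data capture system before these items are asked.
2. If the items stay in the interview, assign a t2 rater who did not hear that participant's t1 answers, where existing staffing allows. Locking the t1 score does not protect a t2 rating made by the same person.
3. State in the protocol how and by whom critical events are collected.
4. Have the interviewer record a guess of the arm and any disclosure after the MADRS is scored, and report both descriptively by arm.
5. Treat any analysis that excludes unblinded ratings as supportive only. Disclosure occurs after randomization and probably depends on arm, so excluding those ratings breaks the randomized comparison.

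**Cost:** a small change to the interview or questionnaire form and one or two added items, with no extra staff. The downside is that recruitment runs in four waves and is listed as ongoing, so waves already assessed would differ from later ones. The date of the change should be recorded and reported.
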